# Effectivity of a mHealth intervention for individuals with obesity: a study protocol for a controlled intervention study

**DOI:** 10.1186/s13102-021-00337-6

**Published:** 2021-09-17

**Keywords:** mHealth, Obesity, Effectivity, Physical activity, Implicit processes, Explicit processes

## Abstract

**Background:**

Obesity is considered an epidemic problem with an increasing number of individuals affected. The physical and psychological complaints associated with obesity point to the importance of implementing effective interventions. Innovative mHealth applications appear to be promising in helping provide a continuous and flexible support during the intervention. Since research on mHealth interventions is still relatively sparse, the main goal of the current study is to assess the effectiveness of an mHealth obesity intervention in terms of weight reduction, health behaviours as well as health-related quality of life. In addition, the study aims to investigate various psychological explicit and implicit processes associated with physical activity behaviour.

**Methods:**

The study includes quantitative and qualitative methods. Regarding the quantitative methods, the goal is to recruit up to 450 individuals at baseline in different obesity centres across Germany with some of these centres offering an mHealth intervention. All individuals who agree to take part in the mHealth intervention will be assigned to the intervention group, while all other individuals will be assigned to the control group. The mHealth obesity intervention consists of three stays at an obesity centre, with approximately six months between stays during which patients are supported by the digital platform CASPAR. The study includes three measurements with a baseline measurement and two follow-up measurements, one after six months and one after twelve months. To assess the effectiveness of the intervention, body weight, physical activity behaviour, eating behaviour as well as health related quality of life will be assessed. In addition, motivation, intentions, self-efficacy, enjoyment, and habit will be used to assess the psychological processes related with physical activity behaviour. A multivariate analysis of variance with repeated measurement and latent growth curve models will be used to compare the development of the variables within the two groups. In relation to the qualitative methods, interviews with individuals of the intervention group will be conducted to shed light on the applicability, acceptance, and usability of the mHealth intervention.

**Discussion:**

This study may provide a valuable insight into the potential of mHealth obesity interventions and the psychological processes related to physical activity behaviour.

*Trial registration* The trial has been registered with the German Register of Clinical Studies (DRKS) on June 30, 2021 under the registration number: DRKS00024836.

## Background

Obesity is considered an epidemic problem, with most European countries projected to have an obesity prevalence of at least 20% by the year 2025 [1]. For instance, in Germany, where the present study will be conducted, the results of epidemiological studies indicate a prevalence rate between 18 and 23% in the adult population [2, 3]. Obesity is associated with a higher risk of physical complaints, such as cardiovascular diseases [4] or type 2 diabetes mellitus [5], as well as mental complaints, such as depression [6] or anxiety disorders [7]. The complaints are not only a burden for the individual, but are also associated with substantial health care costs for the society [8]. Given the health and economic burden associated with obesity, the World Health Organization (WHO) has set the target to halt obesity prevalence at 2010 levels by the year 2025 [9]. However, epidemiological studies indicate that this target is unlikely to be achieved globally [10] as well as in Germany specifically [2].

The trends in the prevalence of obesity underscore the importance of implementing effective obesity interventions. In this regard, the increasing usage of mobile health (mHealth) interventions appears promising in order to reduce sedentary behaviour and to enhance physical activity and healthy eating [11]. mHealth interventions can facilitate access to health care services for a larger portion of the population, provide flexible and rapid feedback to individuals, and tailor interventions to the individuals’ needs [12]. For instance, mHealth interventions can make it easier for individuals to do their exercises in places and at times that are convenient for them. This option can be particularly beneficial for individuals with obesity who often feel uncomfortable in regular fitness settings [13]. However, despite these promising opportunities of mHealth interventions, it is also important to acknowledge their potential challenges. There are several issues, such as doubts about data security, technical difficulties with the software or lack of social support, which may cause individuals to disengage from the intervention [12].

Obesity often results from an imbalance between too little energy expenditure and too much energy intake [14]. Therefore, to achieve weight loss as a primary goal, obesity interventions should help individuals be more physically active and eat healthier. Moreover, various studies indicate that obesity is negatively associated with indicators of health-related quality of life [15]. Individuals with obesity often report that because of their weight they experience physical complaints, have problems during their daily activities, or have difficulties to move in public [16]. In the same vein, individuals with obesity report often experiencing negative affective states, such as anger, fear or shame, in their daily life [17]. Because indicators of health-related quality of life are associated with the use of health services [18] as well as mortality [19], they are also important indicators of the success of an obesity intervention.

To increase the effectiveness of obesity interventions it is further important to understand the psychological processes that are associated with behaviour change [20]. In this study, we focus on the psychological processes related to physical activity. In this regard, a large number of studies shows that individuals who have a more autonomous motivation are more likely to be physically active [21]. In addition, dual-process theories that attempt to explain physical activity behaviour emphasize the role of both more explicit as well as more implicit psychological processes [22, 23]. On the one hand, individuals’ intention, self-efficacy, and enjoyment towards physical activity as more explicit processes have been consistently associated with physical activity [24–26]. On the other hand, habit is considered a more implicit process that has also been shown to be associated with physical activity [27].

To summarize, the high prevalence of obesity is a major problem from both an individual and societal perspective [1]. While mHealth interventions may provide new promising ways to combat obesity, scientific evidence of their effectiveness is still sparse [11]. Therefore, the primary purpose of this study is to evaluate the effectiveness of an mHealth obesity intervention by assessing body weight as well as indicators of physical activity, eating behaviours and health-related quality of life. In addition, the secondary purpose of this study is to assess more explicit (i.e., motivation, intention, self-efficacy, enjoyment) and more implicit (i.e., habit) psychological processes associated with physical activity behaviour change through the use of mixed methods.

### Methods

#### Sampling and participants

The patients are recruited from obesity centres across Germany. Currently, the participants will be recruited from seven obesity centres and it is possible that more obesity centres will participate. Of the seven obesity centres, four offer an mHealth intervention and three do not. The inclusion criteria are that patients are at least 18 years old, have a basic knowledge of the German language, and a BMI ≥ 30. During their first stay at the obesity centre, patients will be asked to participate in the study. Due to the nature of the study, neither participants nor staff can be blinded to allocation. Thus, patients attending an obesity centre that offers an mHealth intervention will be asked whether they want to take part in the mHealth intervention. The patients who agree to take part in such an intervention will be assigned to the intervention group, while those who do not want to take part in such an intervention will be assigned to the control group. Moreover, patients attending a obesity centre that does not offer mHealth interventions will be assigned to the control group. The patients will receive no financial compensation for their participation in the study.

Given the insufficient evidence for the effectiveness of mHealth obesity interventions [28], a small effect size was considered in the power analysis. Conservatively estimating the effect size by *η*^2^ = 0.01, *α* = 0.05, 1-*β* = 0.80, with two groups, a correlation on among repeated measures of *r* = .30 and a design with three repeated measurement occasions, using an ANOVA with repeated measurements (within-between interaction), the calculated total sample size is 225 participants, nearly equally distributed over two groups. Since we expect a dropout rate of about 50% [29], the plan is to recruit 450 patients.

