**Fig. 1 Fig1:**
[figure not shown]
Study design

Demographic information, including age, gender and current employment situation, will be asked at baseline. All other instruments described below will be used at the baseline measurement and the two follow-up measurements. The SPIRIT timetable of the study is presented in Fig. 2.

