### Data analysis

#### Data analysis of quantitative data

All data related to personal information will be pseudo-anonymized. Data will be entered by a research assistant and checked independently for their accuracy by another research assistant. Multiple imputation or the full-information maximum likelihood approach will be employed to treat missing data [47]. We will conduct two analyses: (a) with all patients who agreed to participate in the intervention and (b) with only those patients who completed the intervention (i.e., they had three stays at an obesity centre). A multivariate analysis of variance with repeated measurements (2 groups x 3 time points) will be used to analyze the effects of the intervention on the dependent variables (i.e., body weight, physical activity, eating style & behaviour, health-related quality of life). For the analysis of the structure of determinants of physical activity (i.e., motivation, intention, self-efficacy, enjoyment, habit) and its interdependencies, structural equation modeling procedures will be applied. In particular, the development of the dependent variables will be analyzed using latent growth curve models [48]. Moreover, mediation analyses will be conducted to test whether the determinants of physical activity mediate the effects of the intervention on physical activity behaviour. The effects of age, gender, frequency of participation in the mHealth application (supplied by the provider), and the physical activity level outside of the intervention will be controlled.

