## Discussion

The objectives of this study are (1) to assess the efficacy of an mHealth obesity intervention in terms of weight reduction, health behaviours and health-related quality of life as well as (2) to examine the psychological processes related with physical activity behaviour. Regarding the second objective, psychological processes such as motivation, intention, self-efficacy, habit, and enjoyment will be examined. Moreover, interviews will be conducted to consider patient perspectives on the potential of mHealth interventions for behaviour change.

A look at the alarming trends in the prevalence of obesity [1] highlights the importance of implementing effective obesity interventions. In this regard, although mHealth interventions appear to offer innovative and flexible treatments tailored to the needs of the patients [12], more evidence is needed to assess their effectiveness [11]. In addition, it is important to keep the potential disadvantages in mind, such as technical problems with the software or the lack of social support [12]. One way to counteract these potential issues may be to provide ongoing supervision by a professional support team, as is the case with the mHealth intervention assessed in this study.

A strength of this study is the mix of different methods that may allow to understand the difficulties of individuals with obesity in their behaviour change as well as the potential of mHealth interventions to tackle these difficulties. Moreover, the longitudinal design of the study allows us to examine the trajectories in the outcome variables. On the contrary, a limitation of the study is the lack of randomization, which is not possible for ethical reasons (i.e., patients of the same obesity centre cannot be treated differently). Thus, because patients have the choice to participate in the mHealth intervention, potential selection bias could affect the results. In addition, differences in procedures across obesity centres may confound the effects of the mHealth obesity intervention itself. Finally, it is important to note that COVID-19 could affect the study. In particular, restrictions for obesity centres on patient admissions may impede recruitment of patients as well as their participation in subsequent visits.

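### Patients at the mHealth centres choose their own group, yet age and gender are the only clearly pre-treatment covariates listed; baseline motivation, intention and self-efficacy are not adjusted for in the effectiveness comparison

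*Protocol article*

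**What the plan says.** **Allocation.** Sampling and participants describes patient choice at the four centres that offer the app: "The patients who agree to take part in such an intervention will be assigned to the intervention group". Decliners become controls. So do all patients of the three remaining centres: "patients attending a obesity centre that does not offer mHealth interventions will be assigned to the control group".

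**Effectiveness analysis.** Data analysis of quantitative data states: "A multivariate analysis of variance with repeated measurements (2 groups x 3 time points) will be used to analyze the effects". The outcomes are body weight, physical activity, eating measures and health-related quality of life.

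**Covariates.** The same section ends with a list of four: "The effects of age, gender, frequency of participation in the mHealth application", "and the physical activity level outside of the intervention will be controlled".

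**What is measured at baseline.** Age, gender and employment are recorded at baseline. For the rest, Quantitative data collection methods says: "All other instruments described below will be used at the baseline measurement and the two follow-up measurements". That covers BREQ-2 motivation, intention, self-efficacy, enjoyment and habit. The analysis section places these five in the structural equation, latent growth and mediation models for physical activity.

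**Acknowledgement.** The Discussion concedes that "because patients have the choice to participate in the mHealth intervention, potential selection bias could affect the results". It gives no analytic response.

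**The concern.** When patients choose their treatment, the adjustment set should hold the pre-treatment variables likely to drive both the choice and the outcome. The Background names the obvious candidates: it ties autonomous motivation, intention, self-efficacy, enjoyment and habit to physical activity. Physical activity is one of the effectiveness outcomes and a stated route to weight loss. Accepting CASPAR means agreeing to up to 90 minutes a week between stays, so it is plausible that acceptors and other patients differ on these scales.

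If they do, and if the scales predict how outcomes develop over the year, the group-by-time effect combines the effect of CASPAR with the course that those patients would have followed anyway. The trial is powered for a small effect, so even moderate selection could matter. This is not a detail left to an analysis plan. The article states a covariate list, and that list does not suit a self-selected comparison.

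**Working it through.** **1. The listed covariates, one by one**

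| Covariate | Fixed before treatment? | Addresses self-selection? |
|---|---|---|
| Age | Yes | In part |
| Gender | Yes | In part |
| Frequency of app participation | No; arises after allocation, only in CASPAR users | No; may remove part of the effect |
| Physical activity outside the intervention | Undated; the wording suggests activity during the intervention | Only if it is the baseline value; otherwise may remove part of the effect |

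None of the five psychological constructs is on the list.

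**2. The plan's own sample size**

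Inputs (Sampling and participants): η² = 0.01, α = 0.05, power 0.80, two groups, three occasions, r = 0.30, within-between interaction.

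- f² = 0.01/0.99 = 0.0101, so f = 0.1005.
- Noncentrality λ = f² × N × 3/(1 − 0.30), with df 2 and 2(N − 2).
- The smallest N with power of at least 0.80 is 225 (power 0.802). With 50% dropout, 225/0.5 = 450.

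The stated figures reproduce.

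**3. The 12-month difference this implies**

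If the group difference grows linearly (0, D/2, D), the interaction effects are ±D/4 at the first and last occasions, so f = √(2/3) × D/4. Hence D = 4 × 0.1005/0.8165 = 0.49 outcome SD.

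**4. What the group-by-time test already removes**

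In a simulation of 4,000 trials with 225 patients, r = 0.30, no true effect and a constant group difference of 0.5 SD at every occasion, the baseline-to-12-month contrast was significant at the 5% level in 4.7%. A stable imbalance, in weight for instance, therefore cancels. Only differences in trajectory are left.

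**5. How large trajectory confounding could be**

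The strengths below are assumptions; the article gives none. Let d be the standardised group difference in an unadjusted baseline factor and r_c its correlation with change. One outcome is considered, with 112 and 113 patients and no true effect.

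- SD of change = √(2 × (1 − 0.30)) = 1.183 outcome SD.
- Bias = d × r_c × 1.183.
- SE of the difference in change = 1.183 × √(1/112 + 1/113) = 0.158.
- Rejection rate = 1 − Φ(1.96 − bias/SE) + Φ(−1.96 − bias/SE).

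For d = 0.5 and r_c = 0.3: bias = 0.5 × 0.3 × 1.183 = 0.177; bias/SE = 1.125; rejection rate = 20.3%.

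| d | r_c | Bias (SD) | Share of 0.49 SD | Rejection rate |
|---|---|---|---|---|
| 0.2 | 0.1 | 0.024 | 5% | 5.3% |
| 0.3 | 0.2 | 0.071 | 14% | 7.4% |
| 0.5 | 0.2 | 0.118 | 24% | 11.7% |
| 0.5 | 0.3 | 0.177 | 36% | 20.3% |
| 0.8 | 0.3 | 0.284 | 58% | 43.7% |

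The sign of the bias is the sign of d × r_c, which the article does not determine.

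**The case against.** Four points on the other side deserve an answer.

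**The baseline data are used.** A reader might infer that these measurements go unused. They do not. Weight, GPAQ, the eating scales and SF-12 enter as the first time point of the repeated-measures analysis, and the psychological scales enter the structural equation, growth and mediation models. The complaint that stands is narrower: the psychological scales are not treated as confounders of the effectiveness contrast.

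**Baseline weight is not a good example.** A reader might infer that unadjusted baseline weight biases the result. A stable weight difference cancels in the group-by-time test, so weight matters only so far as it predicts a different course.

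**The list may not be exhaustive, and this is a condensed article.** The covariate sentence closes a paragraph that also covers mediation, and it does not say which model it governs. Fuller adjustment could be specified elsewhere. But the sentence as it stands names what will be controlled, and two of its four items suit a between-group comparison poorly. The outside-activity item would help if it meant the baseline value; the text does not say so.

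**The direction is not established.** A reader might infer that selection favours CASPAR by some number of kilograms. The article links motivation to physical activity, not to acceptance of the app or to weight lost, and it gives no SD of weight change. Patients who expect to struggle alone might be the ones who accept. Controls from the three other centres made no choice and include would-be acceptors, which dilutes any gap between acceptors and decliners.

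The Discussion's admission of selection bias is fair disclosure, but it does not reduce the part of the bias that measured variables could address.

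**Conclusion.** The point holds in a limited form. Group membership at the four mHealth centres is self-selected, and the stated adjustment contains only two clearly pre-treatment variables. Five baseline constructs that the article itself ties to physical activity are left out of the effectiveness model. Confounding of trajectories by these constructs would remain in the group-by-time effect.

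The size cannot be derived from the article. For assumed values of d from 0.2 to 0.8 and r_c from 0.1 to 0.3, the bias ranges from negligible (0.02 SD, error rate 5.3%) to somewhat over half of the implied 12-month difference (0.28 SD, error rate 43.7%). These figures rest on the linear pattern, a single outcome and 225 analysed patients. They show what is possible and do not estimate what will occur. The direction is open.

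The plan should be changed before the data are analysed, since the variables needed are already being collected.

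**What to change.** In Data analysis of quantitative data:

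- State that the between-group effectiveness model is adjusted for, or propensity-weighted on, a compact baseline set: age, gender, employment, baseline outcome values, a BREQ-2 summary score, intention, self-efficacy, habit and enjoyment. Using one BREQ-2 summary rather than its five dimensions keeps the set manageable for about 225 completers.
- If covariates are used in the repeated-measures model, enter them with their interaction with time; a covariate main effect alone does not correct a difference in trajectory.
- Report balance on these variables, before and after weighting if weights are used.
- Keep app frequency, and any activity measured during the intervention, out of this model. If baseline activity was meant, say so.
- Add a comparison of acceptors and decliners within the mHealth centres as a sensitivity analysis. Patients of the three other centres could not receive the app, and by the Control group section those centres differ in length of first stay and in number of further stays. Patient-level weights cannot repair that, so state that between-centre confounding remains.

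**Cost.** Some extra analysis and a small loss of effective sample size; no new variables. The sensitivity analysis will be less precise, depending on how many patients decline. Unmeasured confounding remains.

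**Timing.** The baseline measurement and the introduction to CASPAR both fall in the first stay, in an order the article does not give. It should state whether the questionnaires precede the offer. Requiring that order would be a change in data collection, not only in analysis.

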#### mHealth obesity intervention

The obesity intervention consists of three stays at an obesity centre with about six months between the stays. The first stay lasts three weeks and the two following stays last one week each. The focus for the time at the obesity centres lies on nutritional therapy and exercise therapy, delivered in both individual and group sessions. The stays at the obesity centres are organized by groups. Each new group consists of a maximum of twelve participants. It is intended that a group also stays together for the second and third stay at the obesity centre. However, depending on the patients’ availability, this is not always possible. Moreover, one criterion for another stay is that patients have not gained weight compared to their last stay.

Patients can choose to have a digital supervision during the time between the stays (i.e., patients who do not choose that option can be assigned to the control group). This supervision is applied through the use of the digital platform CASPAR. CASPAR has been developed by the German company “Goreha” and offers exercises as well as seminars to be used digitally (for more information see: https://www.caspar-health.com/en). With relevance for obesity, CASPAR consists of physical exercises, nutritional advices as well as psychological content (e.g., progressive muscle relaxation). Patients will be introduced to CASPAR while still at the obesity centre, and will receive an individualized training plan when they leave the centre. Between each stay, patients are supposed to spend up to 90 min a week with CASPAR for a total of 24 weeks (meaning 2160 min in total). It is up to the patients how they accumulate these minutes (they could do 150 min in one week and 30 min in another week). Only when patients are not active in CASPAR for at least 90 min in six subsequent weeks, the supervision through CASPAR is cancelled. If patients are inactive, they can be encouraged through CASPAR to be active again. Moreover, patients are continuously supervised by qualified therapists. Depending on the obesity centre, this supervision is either done by therapists employed by the provider of CASPAR or by therapists working at the obesity centre. During the intervention, patients can ask the therapists to adapt the exercises when needed. In addition, patients can record themselves when doing the exercises and ask for feedback. In case of possible harm, patients can be referred to appropriate treatment. Moreover, all patients can receive additional therapies depending on their health status.

